Staff conducting pre/post assessments, personnel leading the IVR training and researchers analyzing data are blinded, whereas the personnel administering the stimulation and the project administrators are not. The personnel administering the stimulation is the only person in the room aware of the correspondence between a specific code and stimulation protocol and leaves when the stimulation (either active or sham) is over, thus preventing any influence on training administration. Of note, the electrode placement procedure (see EEG-guided HD-tACS section) is identical for both sham and active stimulation conditions, which helps maintain blinding of both participants and study personnel to treatment allocation, ensuring that the personnel conducting the training remain unaware of the treatment allocation. Unblinding should only occur in rare cases where knowledge of the treatment is crucial for managing the patient, such as in the case of adverse events. Assessments occur at baseline (T0; from one to two days before the beginning of the training), post-treatment (T1; from one to two days after the end of the training), and two months follow-up (T2). All primary and secondary outcomes are assessed at each time point, except for questionnaires on stimulation-induced sensations, which are evaluated after each daily stimulation session, and behavioral, electroencephalographic (EEG) event-related potential (ERP) measures during a cognitive task, which are administered solely at T0 and T1 (see Fig 2).

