**Fig 2 pone.0353955.g002:**
[figure not shown]
Flow chart of patient inclusion.

Both RCT arms are structured as follows. Prior to the beginning of the training (T0), the procedure requires the administration of all primary and secondary outcome measures. Additionally, resting-state EEG is recorded and analyzed to calculate the IGF, which is used as each patient’s specific stimulation frequency delivered through HD-tACS during the IVR training. The treatment is conducted at IRCCS Mondino Foundation for patients with cerebellar malformations and at Ataxia Laboratory at IRCCS Santa Lucia for patients with degenerative cerebellar atrophy. Recruitment began on January 15, 2025 – following Ethics Committee approval but while the formal trial registration was pending due to administrative personnel transitions at the IRCCS Santa Lucia. This decision was taken to meet the stringent project reporting deadlines, which carried non-compliance penalties. Recruitment is expected to conclude on December 14, 2026. Data collection will continue through the follow-up period, ending two months after the last participants are enrolled, in February 2027. Results are expected to be available by April 2027, a few months after data collection is completed. The authors confirm that all ongoing and related trials for this intervention are registered.

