
Primary outcomes are assessed at all time points (T0, T1, T2). Among secondary outcomes, the DRT and EEG recordings are conducted at baseline (T0) and immediately after training (T1). Neuropsychological evaluation, VABS-II, and CPM47 are administered at each time point.

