### Sample size calculation

Using the GPower 3 software [70] with the “as in SPSS option”, we estimated that, with a mixed design between (group factor: active group vs. sham group) – within (Time points: T0, T1, T2, numerator DF = 2), a sample of 15 subjects per group allows detecting moderate to large effects (f (U)=0.428), based on previous study of the effects of cerebellar electrical stimulation on action prediction tasks in patients with cerebellar malformation [32] with a power of 0.80, setting a significance threshold of 0.05. Hence, 30 CM patients and 30 CA patients will be recruited.

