Linear mixed models (LMMs) will be used to treat data considering each primary outcome measure as a dependent variable in separate models. Treatment (active vs. sham HD-tACS as between-subjects variable), time (T0, T1, and T2) and their interactions will be entered as fixed factors, while patients included will be entered as random factors. To take into account a-priori sample differences (even if not statistically significant), we will also consider the age and IQ of participants as possible covariates in follow-up analyses. If one of these covariates will result statistically significant, data will be stratified according to homogeneous values of the significant variable and a secondary analysis will be conducted on homogeneous subgroups for clarifying the effect of the covariates, correcting the alpha level to avoid the possible inflation of first type error. A significance threshold of *p* = 0.05 will be set for all analyses. Post-hoc comparisons will be performed only on statistically significant factors to identify the significant difference between the levels of the independent variables, applying multiple correction methods for type I error. In case of not normally distributed data, the first approach will be the adoption of techniques to normalize data such as the use of z-scores or percentage points; if these kinds of normalization fail, data will be summarized and analyzed by using non-parametric statistics. Data will be reported in terms of median values and quartiles. Instead of LMMs, Kruskal-Wallis analysis for between-subject comparisons will be adopted, together with Friedman’s analysis to compare within-subject parameters. All the analyses will be performed at the end of all T1 evaluations, and no interim analyses will be performed.

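### The analysis is timed to the last T1 visit, although the efficacy model, the sample size and the trial calendar all need T2; probably a slip, but it misdates the primary analysis

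*Protocol article*

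**What the plan says.** In the protocol article, the Statistical analyses section closes with the timing rule: "All the analyses will be performed at the end of all T1 evaluations, and no interim analyses will be performed". Earlier in that section the linear mixed model for each primary outcome is specified with treatment and time, where "time (T0, T1, and T2) and their interactions will be entered as fixed factors".

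Other parts of the article bear on the same point:

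- **Sample size calculation:** the design is a between-within one with "Time points: T0, T1, T2, numerator DF = 2", and "a sample of 15 subjects per group allows detecting moderate to large effects (f (U)=0.428") "with a power of 0.80, setting a significance threshold of 0.05".
- **Study design (assessments):** the last assessment is described as "and two months follow-up (T2").
- **Secondary outcomes (closing paragraph):** "Primary outcomes are assessed at all time points (T0, T1, T2"). Only the discrimination response task and the EEG recordings stop at T1.
- **Study design (calendar):** recruitment runs from 15 January 2025 to 14 December 2026. "Data collection will continue through the follow-up period, ending two months after the last participants are enrolled, in February 2027". Results are expected by April 2027, once collection is complete.
- **Statistical analyses (analysis set):** patients with at least one evaluation are included, and missing data are not imputed.

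**The concern.** The timing rule is an affirmative, universal statement, not a detail left for a fuller document. It covers all analyses, is not limited to the measures that end at T1, and no separate T2 analysis is described. At the last T1 visit, patients treated in the preceding two months have not reached T2, so the pre-specified treatment-by-time test on three levels would be run on an incomplete third level.

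Three things are at stake. Some T2 data would be left out of the primary test. Results by arm could be known while the remaining T2 assessments are still to be done. And the date of the primary analysis would be open to argument: a report made at T1 could cite the timing sentence, and one made at T2 could cite the model, each as pre-specified.

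**Working it through.** **1. Reproduce the stated power.** Inputs from Sample size calculation: k = 2 groups, m = 3 times, N = 30 per cohort, f(U) = 0.428, alpha 0.05, and the SPSS option in G*Power. Sphericity is assumed.

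- df1 = (k − 1)(m − 1) = 1 × 2 = 2, which matches the stated numerator df
- df2 = (N − k)(m − 1) = 28 × 2 = 56
- noncentrality = f(U)² × df2 = 0.1832 × 56 = 10.26
- power from the noncentral F distribution = 0.804

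N = 29 gives 0.787, so 30 is the smallest N that reaches 0.80. The stated figure reproduces, and it does so with three time points. T2 is therefore part of the basis for the sample size.

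**2. When the literal trigger would fall.** Assume that the last patient has T0 on the final recruitment day and sessions on consecutive days. The article puts T0 one to two days before training, has eight daily sessions, and puts T1 one to two days after. T1 then falls 9 to 11 days after 14 December 2026, that is 23 to 25 December 2026. T2, two months on, falls on 23 to 25 February 2027. The literal trigger thus comes about two months before the article's own end of data collection.

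**3. How many patients would lack T2.** 15 January 2025 to 14 December 2026 is 698 days. Assume even accrual and a gap of about 61 days from T1 to T2.

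- Per cohort: 30 × 61 / 698 = 2.6 patients
- Both cohorts: 60 × 61 / 698 = 5.2 patients, or about 9%

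Late-loaded accrual would raise these numbers. The article gives no accrual curve.

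**4. What that costs in power.** Count only patients with all three visits, with f(U) and alpha unchanged.

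| Patients per cohort with T2 | df2 | Noncentrality | Power |
|---|---|---|---|
| 30 (as planned) | 56 | 10.26 | 0.804 |
| 27 (even accrual, 30 − 2.6 rounded down) | 50 | 9.16 | 0.752 |
| 24 (assumed late-loaded accrual) | 44 | 8.06 | 0.689 |

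The last two rows are lower bounds for the planned mixed model, because it keeps the T0 and T1 data of patients whose T2 is pending. Under even accrual the power lies between 0.752 and 0.804.

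**5. The statements side by side.** Five elements need or assume complete T2 data: the model, the sample size, the primary outcome schedule, the data-collection end date, and results following completed collection. One sentence points to T1. The ban on interim analyses in that same sentence also fits only an analysis made after collection has ended.

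**The case against.** The strongest reply is that this is a one-character slip. Every other statement points to analysis after T2, and the calendar puts results after completed collection. That is probably right and it limits the weight of the point. It does not remove it: the sentence is the only one that says when the analysis is triggered, and the article commits its authors to following the procedures as presented.

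It can also be said that the missing T2 values would be administrative. They follow from enrolment date, not outcome, and blocked 1:1 randomization should roughly balance them between arms. A likelihood-based mixed model uses the T0 and T1 data that these patients have. This stands: the cost is mainly precision, not bias. Likewise, by the last T1 visit every patient has been randomized and treated, so an early look could not alter allocation or treatment. Assessors and analysts are blinded, and an aggregate result does not reveal an individual's arm. What remains is a possible expectation effect on the outstanding T2 assessments.

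Three stronger readings are tempting, and the documents do not support them:

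- **An inflated type I error.** A reader might infer two unadjusted looks, one at T1 and one at T2. No second analysis is planned, so inflation would arise only if the analysis were later repeated.
- **T2 dropped altogether.** With two time points and the same f(U), power would be 0.590 (df1 = 1, df2 = 28). But the model names T2 explicitly, so nothing indicates that it would be discarded.
- **A wrong end date for collection.** A reader might object that T2 falls later than two months after the last enrolment. On the schedule in the article it falls about 9 to 11 days later, still within the stated month of February 2027.

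**Conclusion.** The contradiction is real and needs correcting. The timing sentence conflicts with the three-level efficacy model, the three-time-point sample size, the primary outcome schedule and the trial calendar. T1 is most likely an error for T2, though the article does not settle this.

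Followed as written, the primary test would lack T2 for about 2.6 of 30 patients per cohort, and power would lie between about 0.75 and the stated 0.80. These figures assume even accrual in each cohort over the whole recruitment period, a gap of about 61 days from T1 to T2, sphericity, and the plan's own f(U). The analysis would also be an early look in all but name. The importance lies in fixing the date of the primary analysis unambiguously; the numerical loss is modest, and the sample size itself is sound on its stated inputs.

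**What to change.** Replace the timing sentence with wording such as: all efficacy analyses will be performed once, after the last T2 evaluation and database lock, and no comparison between treatment arms will be made before then.

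If an analysis at T1 is in fact intended, define it separately: its outcomes and model, its share of alpha, who sees the results, and how the staff doing the remaining T2 assessments are kept from them. The statement that there are no interim analyses would then have to be changed as well.

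The cost is one sentence, to be settled before any comparison by arm is made. The sample size does not change (power 0.804 with 30 per cohort and three time points). With the last T2 visit expected in February 2027, the April 2027 results date still holds.

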### Data safety and management

The project entails the processing and storage of pseudonymized data, which are securely archived in a centralized repository situated on the servers of the study sponsors. Questionnaire scores and neuropsychological test results do not include any personal information regarding the participants, who are distinguished solely by an alphanumeric code. Any records containing names or other personal identifiers, including informed consent forms, are stored separately from the study records identified by code number. Access to the archives is strictly controlled and granted solely through a rigorous authentication procedure, ensuring appropriate usage rights are maintained.

### Ethics and dissemination

Approval for this study was granted by the local ethics committees (Comitato Etico Pavia, Prot. N. 0025455/23, approved on May 15, 2023; Comitato Etico Fondazione Santa Lucia Roma, Prot. CE/2023_001, approved on January 31, 2023). Written informed consent is obtained from the parents or legal guardians of minors, and directly from adult participants. Minors as well are asked to give their assent for participation. Subjects are discontinued in the case of serious adverse events. Important protocol modifications will be reported to the Italian Ministry of Health, and approved by the Ethics Committees.

Patients and the public were not involved in the design of the study nor are involved in its conduct, while patients’ associations will be involved in the dissemination plans of the results. The outcomes of this study will be shared with the involved physicians, referring practitioners, patients, and the broader medical community. Presentation of results is planned at academic and/or clinical conferences. Furthermore, the study aims to produce at least one peer-reviewed publication of quantitative findings in a reputable national or international medical journal. Reporting of this RCT will adhere to CONSORT guidelines [71] to ensure transparency and completeness in the presentation of results. The authors will adhere to principles of transparency and reproducibility in research by following the procedures presented in this study protocol and by sharing research material and anonymized dataset of this study in public repositories (https://osf.io/).

## Discussion

The role of the cerebellum has been radically redefined in recent decades, extending its functional domain well beyond motor control. It is now widely acknowledged as a critical node within the distributed neural networks subserving cognitive and social processing [72,73]. However, despite this increasing neuroscientific knowledge, only a limited number of studies have addressed the rehabilitation of CCAS so far [7,21,22]. One of the first and few attempts in this direction utilized VR; specifically, a recent study on patients with cerebellar malformations showed that a VR intervention targeting social prediction was effective not only in enhancing these functions but also in producing effects generalizable to standard measures of theory of mind and inhibitory control [21]. A promising and complementary avenue for the further potentiation of these skills is represented by cerebellar neuromodulation. While neuromodulation has already demonstrated feasibility and safety across various neurological and psychiatric populations, even reducing social-affective symptoms in some instances [26,28,29], its application in patients with primary cerebellar damage has remained focused almost exclusively on motor recovery [26]. Despite this traditional focus, preliminary data suggest that cerebellar neuromodulation could be a key modality for boosting social prediction abilities [32], highlighting the therapeutic potential of integrating such innovative approaches to rehabilitate social skills in this population.

Based on this theoretical framework and the encouraging preliminary findings, the aim of the present protocol is to present a novel, multimodal therapeutic approach specifically designed to address the cognitive and social deficits characterizing patients with cerebellar alterations. Crucially, this protocol advances previous methodological approaches through specific innovations regarding both the behavioral and neuromodulatory components. Unlike previous protocols (e.g., [21]), this protocol employs an IVR system to maximize patient engagement and the sense of presence, promoting a higher degree of embodiment. By simulating realistic social scenarios, IVR enhances the ecological validity of the training, thereby facilitating the transfer of acquired social prediction skills to real-life interactions. Concurrently, regarding the neuromodulation component, this protocol moves beyond traditional approaches (e.g., TMS or tDCS) by utilizing tACS. While cerebellar tACS has been applied almost exclusively to investigate and enhance motor functions so far (see [33]), it offers a unique advantage. Instead of merely exciting or inhibiting neuronal excitability (as for instance tDCS), tACS allows for the modulation of the intrinsic oscillatory behavior of the target area. This mechanism is critical for promoting neuroplasticity within the cerebro-cerebellar circuits, as it can exert effects on distal cortical regions functionally connected to the cerebellum [38]. Therefore, by synergistically combining the ecological potential of IVR with the network-level modulation of tACS, our protocol aims to provide the first mechanism-based rehabilitation for social prediction in cerebellar patients.

We hypothesize that the simultaneous application of IVR training and HD-tACS will yield synergistic effects, exceeding the benefits of single-modality interventions. Specifically, IVR provides the crucial experiential context: by ensuring a highly embodied experience and a strong sense of presence, it actively recruits the predictive coding mechanisms required to generate and update internal models of social interactions. Simultaneously, cerebellar HD-tACS modulates the underlying neural substrate to facilitate this relearning process. By entraining intrinsic neuronal oscillations, tACS aims to regulate the functional connectivity of cerebello-cerebral circuits, creating an optimal neurophysiological state for plasticity. Thus, we expect that tACS will potentiate the training effects induced by IVR, leading to a more robust restoration of social prediction abilities and better generalizability to daily life functioning.

A critical methodological advancement of this protocol is the implementation of a personalization strategy, fully aligning with the paradigm of precision medicine. First, regarding the behavioral training, we adopted a patient-centered approach to maximize motivation and compliance. The IVR content includes a set of diverse social scenarios and avatars that are specifically adapted to the patient’s age and everyday social scenarios. This ensures that the immersive experience is not only ecologically valid but also highly engaging. Complementing this behavioral tailoring, the neuromodulatory component is physiologically personalized. Building on evidence that tACS is most effective when matching endogenous rhythms (Arnold tongue principle) [74], we utilize EEG-guided IGF. Since gamma oscillations reflect the basal firing rate of Purkinje cells, locking the stimulation to the patient’s specific IGF ensures that the external current enhances rather than overrides intrinsic network dynamics. By tailoring both the immersive experience and the neurophysiological parameters, we aim to create a therapeutic environment that is uniquely adjusted to the individual needs of each patient.

Furthermore, the inclusion of both patients with CM and CA offers a unique opportunity to validate this multimodal approach across distinct neurophysiological substrates. While the differing developmental trajectories of these groups suggest divergent network organizations, a key objective is to evaluate whether these distinct etiologies differentially modulate the responsiveness to the proposed multimodal treatment. Specifically, in CM patients, the intervention interacts with neural circuits that have undergone atypical organization and compensatory rewiring since early life. In contrast, in CA patients, the treatment aims to counteract the degradation of previously established networks. By applying the same plasticity-inducing protocol (i.e., tACS + IVR) to these diverse pathological models, we can thus determine the extent to which the timing of the cerebellar damage—developmental versus acquired—influences the susceptibility to neuromodulation and the overall potential for functional restoration.

Importantly, this study addresses the critical issue of cerebellar tACS feasibility in pediatric populations. By adopting safety parameters tailored to adolescent anatomy (i.e., intensity limited to 1 mA), we aim to establish the tolerability of this technique in developing brains. Concurrently, to ensure the intervention’s applicability across varying levels of cognitive functioning, we recruit patients with moderate intellectual disability alongside those with mild or no impairment. This inclusive approach ensures the generalizability of results to a more representative sample of the cerebellar malformation population. Proving the viability of neuromodulation in this diverse group is a prerequisite for extending NIBS interventions to developmental disorders, potentially accelerating the adoption of cognitive rehabilitation across the lifespan.

On a broader scale, the present protocol embraces a transdiagnostic perspective that extends well beyond cerebellar disease. This approach is grounded in recent evidence suggesting that structural alterations within cerebellar circuitry are associated with a general liability for common mental disorders [75]. Consequently, validating a protocol that targets these specific circuits could identify therapeutic targets relevant for a wide range of conditions linked to cerebellar dysfunction, including neurodevelopmental (e.g., Autism Spectrum Disorder), neurological (e.g., Alzheimer’s disease, Parkinson’s disease), and psychiatric (e.g., Schizophrenia, mood disorders) conditions. In this light, the present protocol aims to lay the groundwork for the development of integrative interventions, translating cutting-edge findings in experimental neuroscience into rehabilitation procedures capable of offering long-lasting benefits in everyday life.

It is necessary, however, to acknowledge some limitations. First, a significant challenge stems from the anatomical heterogeneity inherent to the studied populations. In both malformative and degenerative patients, structural alterations are neither homogeneous nor precise, which may introduce variability in the neurophysiological response and limit anatomical standardization. In a related vein, although E-field modeling was performed to optimize the tACS montage, inter-individual anatomical variability (e.g., skull thickness, cerebellar geometry) might still influence the precise current distribution, a common constraint in non-invasive brain stimulation studies. Finally, regarding the IVR component, although severe ataxia is not a primary feature of our sample, the potential presence of mild vestibular or postural deficits in some patients could still pose a risk of cybersickness. To mitigate this, we have adopted specific safety measures, including seated administration of all sessions, frequent rest breaks, and constant monitoring of patient comfort.

In conclusion, the proposed protocol represents the first systematic attempt to translate the theoretical framework of cerebellar internal models into a concrete rehabilitation strategy. By synergistically targeting the neural and behavioral components of social prediction, this protocol aims not only to validate a novel therapeutic tool for cerebellar patients but also to provide crucial insights into the functional plasticity of the cerebellum. Ultimately, improving social prediction abilities holds the promise of restoring the behavioral fluidity necessary for successful social interactions, significantly impacting the quality of life of patients for whom specific treatments are often unavailable.

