Building on this evidence, the present protocol aims to investigate the combined effects of a neuromodulation protocol—designed to facilitate cerebello-cerebral plasticity—and Immersive Virtual Reality (IVR) training targeting internal models of social events. The study involves early adolescents and adults with congenital non-progressive cerebellar malformations, as well as adults with neurodegenerative cerebellar disorders. To maximize efficacy, the intervention leverages previous findings suggesting that weak exogenous electrical stimulation effectively modulates neural oscillations only when matching endogenous rhythms [36]. Consequently, rather than overriding intrinsic dynamics, we aim to enhance them using a personalized High-Definition (HD)-tACS protocol. Specifically, stimulation will be delivered at each participant’s Individual Gamma Frequency (IGF). We hypothesize that coupling this personalized stimulation with IVR-assisted social prediction training will potentiate treatment outcomes by promoting brain plasticity and boosting cognitive learning. Furthermore, including both congenital and progressive conditions allows for the evaluation of distinct pathological models. While congenital malformations impact neural development and the functional organization of circuits during highly plastic early stages, neurodegenerative disorders affect fully established networks. Comparing these groups offers a unique opportunity to investigate the plasticity of cerebello-cerebral social circuits, revealing specific anatomo-functional associations and distinct recovery potentials. Ultimately, this transdiagnostic approach may identify critical therapeutic targets for improving socio-cognitive abilities in other conditions linked to cerebellar dysfunction, such as Autism Spectrum Disorder, dementia, and mood disorders [42–44].

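### Differential response of the two populations is called a key objective, but the stated model has no population term and the sample size does not cover the comparison

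*Protocol article*

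**What the plan says.** The Discussion states that "a key objective is to evaluate whether these distinct etiologies differentially modulate the responsiveness to the proposed multimodal treatment". It goes on: "we can thus determine the extent to which the timing of the cerebellar damage—developmental versus acquired—influences the susceptibility to neuromodulation". The Introduction announces the same comparison: "Comparing these groups offers a unique opportunity to investigate the plasticity of cerebello-cerebral social circuits".

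Statistical analyses defines the efficacy model for each primary outcome: "Treatment (active vs. sham HD-tACS as between-subjects variable), time (T0, T1, and T2) and their interactions will be entered as fixed factors". Patients are the random factor. Age and IQ are possible covariates in follow-up analyses. Population (cerebellar malformation, CM, or cerebellar atrophy, CA) is not among the terms.

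Sample size calculation uses two groups (active, sham) and three time points, with 15 per group, f(U) = 0.428, alpha 0.05 and power 0.80. It applies the result to each population, giving 30 CM and 30 CA.

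On setting, Study design says: "The treatment is conducted at IRCCS Mondino Foundation for patients with cerebellar malformations and at Ataxia Laboratory" for those with atrophy, at a second institute.

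On the combination, the Discussion hypothesises that "the simultaneous application of IVR training and HD-tACS will yield synergistic effects, exceeding the benefits of single-modality interventions". Under Study design every participant receives IVR, and only active versus sham tACS is randomised.

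**The concern.** Whether CM and CA respond differently is a question about the difference between two treatment effects, so it needs a Population x Treatment x Time term or an equivalent contrast. The stated model estimates a treatment effect but no difference between populations, and the sample size was not set for such a difference.

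Without a named contrast, the obvious fallback is to set the two within-population results side by side and note which one is significant. That is not a valid comparison. At stake is a conclusion that the article calls a key objective and says the trial can determine. An interaction test added after the data are seen would look post hoc.

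**Working it through.** **Inputs.** From Sample size calculation: f(U) = 0.428, 15 per group, three time points, numerator df 2, alpha 0.05, power 0.80, 30 + 30 patients. From Study design: 1:1 allocation, one site per population, strata. From Patients selection: age and IQ limits. Assumed here: sphericity, equal variances in the two populations, no dropout. The value 0.428 is taken as stated.

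**Step 1. Reproduce the plan's figure.** With the G*Power option named in the plan, lambda = f(U)² x (N − 2) x (3 − 1).
- lambda = 0.428² x 28 x 2 = 10.26, with df 2 and 28 x 2 = 56.
- Power = 0.804, and 30 is the smallest N that reaches 0.80.

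The stated sample size is correct for its own contrast.

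**Step 2. Power of the between-population contrast at N = 60.** The difference between two independent, equally sized treatment effects has twice the variance of one effect. If the populations differ by r times the planning effect, lambda = 10.26 x r² / 2, with df 2 and (60 − 4) x 2 = 112.

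| Difference (multiple r of planning effect) | lambda | Power |
|---|---|---|
| 0.5 | 1.28 | 0.16 |
| 1 | 5.13 | 0.50 |
| 1.39 | 9.91 | 0.80 |
| 1.5 | 11.54 | 0.86 |
| 2 | 20.52 | 0.985 |

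The case r = 1 is, for example, the full planning effect in one population and none in the other. The value r = 1.39 corresponds to f(U) of about 0.59 on the single-population scale.

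**Step 3. Sample size for 0.80 power on this contrast.** With n per cell, lambda = 0.428² x 2 x (2n − 2) x r² / 2.
- r = 1: n = 28 per cell, 112 patients.
- r = 0.5: n = 107 per cell, 428 patients.

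**Step 4. Illustration only: side-by-side p-values.** If both populations had the same true effect and each test had power 0.80, exactly one would be significant in 2 x 0.80 x 0.20 = 32% of trials.

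**Step 5. What travels with population.**
- Site: fully aligned. Treatment is randomised within site, so a site main effect cancels. Only a site-by-treatment effect would bias the comparison.
- Age: CM 12–32, CA strata 18–68. There is planned overlap: three of the six CM blocks of five are adults (3 x 5 = 15, aged at most 32), and 15 CA patients are to be 18–35.
- IQ: CM at least 50, CA at least 75. Two of the six CM blocks (2 x 5 = 10) have IQ above 80.

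**Step 6. Synergy wording.** The randomised conditions are IVR + active and IVR + sham. Their difference is the effect of tACS added to IVR. Superiority to tACS alone needs a tACS-without-IVR condition. Synergy as an interaction also needs a condition with neither. The design has neither of these.

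**The case against.** **The design is sound for this contrast.** A reader might infer that the trial cannot compare the populations at all. That is not so. Both are randomised active versus sham, with the same stimulation and the same visits, so the contrast can be estimated from the planned data. What is missing is the analysis term.

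**No passage says that separate p-values will be compared.** This is true. The document gives no method for the comparison, so the 32% only shows why a method should be named. It does not describe the plan.

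**The article is condensed and an unseen SAP may hold the analysis.** This carries some weight, since models are specified only for primary outcomes. But the article lists its model terms and its sizing design explicitly, and neither matches what it calls a key objective. An SAP cannot remove the alignment with site.

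**Confounding by age and IQ can be overstated.** This also stands. The ranges overlap by plan, and age and IQ are already candidate covariates with subgroup follow-up. The alignment is partial.

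**Power of 0.50 is not a ceiling.** One might read it as the best the trial can do. It applies to a difference of one planning effect. Larger differences, such as effects in opposite directions, would be detected with high power.

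**The synergy claim is partly testable.** IVR + sham is the IVR-only comparator, and the same Discussion paragraph also states the expectation in testable form, as tACS strengthening the training effect. Only the stronger wording goes beyond the design.

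**Conclusion.** The point holds as a mismatch between a stated objective and the stated analysis. The efficacy model has no population term, the sample size covers one population at a time, and yet the Discussion promises to determine the influence of the timing of damage.

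Once the term is added, the test remains weak for plausible differences: about 0.50 for one planning effect and 0.16 for half. These figures rest on the assumptions listed in the working. Because site is inseparable from population, even a clear difference could not be put down to timing of damage with confidence. An exploratory comparison is what the data can support.

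The active-versus-sham analysis within each population is untouched. The synergy sentence is a minor matter of wording. The change should be made, but the trial's main result does not depend on it.

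**What to change.** 1. Pre-specify one pooled model with Population x Treatment x Time, labelled exploratory. Report the between-population difference in treatment effect with its 95% CI.
2. State that no cross-population conclusion will rest on separate within-population p-values.
3. State the power: about 0.50 for a difference of the full planning effect, about 0.16 for half, and 0.80 at roughly 1.4 times, under sphericity and no dropout.
4. In the Discussion, replace the claim to determine the influence of timing with an exploratory comparison. Name site as fully aligned with population (biasing only through site-by-treatment modification) and age and IQ as partly aligned.
5. Reword the synergy hypothesis to say that active tACS adds to IVR training compared with sham tACS plus IVR.

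The cost is one extra model on data already being collected, and a narrower stated claim. Recruitment is expected to run to December 2026, so this can be fixed before analysis.
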